### Safety and adverse events

Any serious adverse effects that occur in the study period should be recorded. If adverse events occur, the investigator will determine whether the participant should withdraw from the study, according to the condition of the patient. For serious adverse events, the investigator must immediately take necessary measures and report to the investigator and the ethics committee. Serious adverse effects that are still ongoing at the end of the study period must be followed up to determine the final outcome.

### Data collection and management

Patient information will be entered into the paper case report forms (CRFs) promptly and synchronously with input into the electronic CRF. The occurrence of unexpected problems during this process should be recorded, and will be informed in a timely manner.

In order to ascertain the two randomized groups are similar, the demographic/disease characteristics including sex, age, region, body mass index (BMI) and medical history will be collected.

The committee that was responsible for the study design and the implementation process will ensure the effectiveness and integrity of the trial design. The committee will supervise the integrity and accuracy of data collection to control its quality. The committee also needs to evaluate key outcomes based on the clinical expertise of its members.

Data sharing is not applicable to this protocol article as no datasets have as yet been generated or analyzed during the current study. The results should be made public within 24 months of reaching the end of the study. The end of the study is the time point at which the last data items are to be reported, or after the outcomes of data are sufficiently mature for analysis as defined in the statistical analysis section. A full report of the outcomes should be made public no later than 3 years after the end of the study. Results will also be available through the Clinical Trials Registry.

Missing data will be reviewed to identify potential patterns, and examined to assess how these patterns impact our results. There are three types of missing data that can occur when the data are being collected [13]. When data are missing (completely) at random, unbiased results can still be obtained using the maximum likelihood method that will be used in the linear mixed model analysis. When data are not missing at random, we will analyze sensitivity using pattern mixture models and the results will be used to assess the impact of missing data on the reported conclusions.

### Statistical analysis

Statistical analysis will be performed using SPSS software 11.0. The primary analysis will be conducted on the intention-to-treat principle. Descriptive analysis (calculations of averages, frequencies, proportions, or rates) will be conducted. Comparisons will be made using Student’s *t* test or the Mann–Whitney *U* test for comparison of continuous variables and Pearson’s *χ*^2^ test for dichotomous variables. Student’s *t* test will be used to compare variables of normal distribution. The Mann–Whitney *U* test will be used to compare variables of non-normal distribution. The chi-square test or Fisher’s exact test will be used for comparison of categorical variables between the two groups. Survival functions will be estimated using the Kaplan-Meier method and will be compared using the log-rank test. The medical costs will be retrospectively calculated for the patients involved in a prospective randomized controlled trial and will be compared in a post hoc analysis of the two groups. The Wilcoxon matched pairs test will be used to compare the medical costs between the RIF and ATO groups. All statistical tests will be two-sided, and the level of significance will be set at 0.05, except for the non-inferiority hypothesis.

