## Methods

### Study hypothesis

The hypothesis is that ATRA-RIF is not inferior to ATO-ATRA in treating non-high-risk APL. Application of oral RIF may reduce the total hospitalization days and medical costs. The simultaneous application of oral RIF and ATRA is more convenient for patients and improves the efficacy.

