### Sample size calculation

On the basis of the previous studies [4, 9, 11] assuming 97% DFS in the control (ATO) group, and conservatively assuming 99% DFS in the experimental (RIF) group, a noninferiority margin of − 5%, follow up of 2 years, 5% type I error (one-sided), 90% power, we used PASS 11 to calculate a required sample size of 53 evaluable patients per group to draw a conclusion of non-inferiority. Allowing for a withdrawal rate of 10%, 59 patients per group will be required. Therefore, we plan to enroll 118 patients into two groups (1:1). We plan a final analysis only, with no interim analysis. The design of this trial is a non-inferiority trial with superiority being explored if non-inferiority is identified.

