#### Relapse is defined as follow [12]:

Hematologic relapse is defined by bone marrow blasts of 5%, reappearance of blasts in the blood, or development of extramedullary disease. Molecular relapse: if studied pre-treatment it is defined by recurrence of minimal residual disease (MRD) as assessed by quantitative RT-qPCR or by multi-color flow cytometry.

The secondary outcomes of this trial are hospitalization days and medical costs in the two arms. The medical costs will be calculated for each patient. The hospitalization costs for induction and consolidation therapy will be calculated for inpatients. The hospital costs for induction therapy and consolidation therapy will be calculated for outpatients. All medical costs can be collected and multiplied by the unit cost of each resource use. After the patient is discharged from the hospital, we can obtain the medical costs from the medical record in hospital according to the patient’s name/case number. For the outpatients, the medical costs can be obtained from the outpatient system after the patient’s visit. Hospitalization days will be recorded over a 10-month time frame.

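### Medical costs, and hospital days if non-normal, are compared by rank tests, which neither test nor estimate the reduction in total cost and days that the trial sets out to show

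*Protocol article*

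**What the plan says.** The secondary outcomes are named under Outcome measures, in the text that follows the relapse definitions: "The secondary outcomes of this trial are hospitalization days and medical costs in the two arms". The same text builds costs patient by patient ("The medical costs will be calculated for each patient"), limits them to induction and consolidation therapy, and counts hospital days over 10 months. The Study hypothesis section states what these outcomes should show: "Application of oral RIF may reduce the total hospitalization days and medical costs". The Discussion paragraph of the Abstract repeats this as an aim.

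The Statistical analysis section gives two rules that matter here.

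- **Costs** have their own sentence, with no condition on normality: "The Wilcoxon matched pairs test will be used to compare the medical costs between the RIF and ATO groups".
- **Other continuous variables**, which include hospital days, go by distribution. Student's t "test will be used to compare variables of normal distribution", and the Mann-Whitney U "test will be used to compare variables of non-normal distribution".

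On the level: "All statistical tests will be two-sided, and the level of significance will be set at 0.05, except for the non-inferiority hypothesis". Averages appear only as descriptive analysis. No test of, or interval for, a difference in mean cost is stated.

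**The concern.** Total cost in an arm is mean cost times the number of patients, so a claim that RIF reduces total cost is a claim about means. A rank test responds instead to how often a RIF patient costs less than an ATO patient. The two questions have the same answer when the cost distributions have the same shape. They can differ when one arm has a longer tail, because ranks discount the few expensive patients who carry much of the total.

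Unequal shapes are plausible here. The main Discussion says that RIF patients are treated at home during remission therapy and ATO patients in hospital. ATO cost would then follow the schedule closely, while RIF cost would be low unless a complication led to admission.

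Two things are at stake. A significant result could be read as lower cost when average cost is the same. And even a correct result would come without an interval for the amount saved per patient. For days, the normality rule also lets the observed data choose whether means or ranks are compared.

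**Working it through.** **Plan's own figure.** None is given for costs or days. The planned size is 53 evaluable per arm; with 10% withdrawal, 53 / 0.9 = 58.9, so 59 per arm and 2 × 59 = 118. I use n = 59 and a two-sided 0.05 level.

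**Assumed inputs.** The documents give no spread for cost. I assume lognormal costs with equal means, ATO coefficient of variation (CV) 0.3 and RIF CV 0.6 to 1.0.

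**Step 1: log-scale variance**, s² = ln(1 + CV²).
- CV 0.3: ln(1.09) = 0.086
- CV 0.6: ln(1.36) = 0.307
- CV 1.0: ln(2.00) = 0.693

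**Step 2: chance that a RIF patient costs less than an ATO patient at equal means**, P = Φ[ ½(s²_RIF − s²_ATO) / √(s²_RIF + s²_ATO) ].
- RIF CV 0.6: 0.111 / 0.627 = 0.176, P = 0.57
- RIF CV 1.0: 0.303 / 0.883 = 0.344, P = 0.63
- Equal CVs: P = 0.50

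**Step 3: approximate Mann-Whitney rejection.** The null standard deviation of the estimated P is √[(2n + 1) / (12n²)] = √(119 / 41,772) = 0.0534.
- RIF CV 0.6: 0.070 / 0.0534 = 1.31; Φ(1.31 − 1.96) ≈ 26%
- RIF CV 1.0: 0.134 / 0.0534 = 2.51; Φ(2.51 − 1.96) ≈ 71%

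**Step 4: simulation**, same assumptions, equal means, 59 per arm. The rank-test rejections are nearly all in favour of RIF.

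| Test | Rejection, RIF CV 0.6 to 1.0 |
|---|---|
| Wilcoxon signed-rank on arbitrary pairs (as written for costs) | about 12% to 32% |
| Mann-Whitney (the general rule, once pairing is removed) | about 28% to 72% |
| Welch on means | about 5% to 7% |

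The hand approximation agrees with the Mann-Whitney row. With identical distributions all the tests stay near 5%.

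**Step 5: a mean in the wrong direction.** With log-SD 0.8 for RIF, 0.3 for ATO and RIF mean cost 15% higher, Mann-Whitney still favours RIF in 23% of trials and the signed-rank test in about 5%.

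**Step 6: shared induction cost.** Both arms receive the same induction. If it makes up half of total cost (assumed), Mann-Whitney falls to about 9% to 30%. The reduction comes from patient-to-patient variation in induction cost, which blurs the difference in shape. A constant added to both arms would leave every rank unchanged, and a smaller induction variation reduces the excess less. This shows a direction, not a firm size.

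**Step 7: days.** Under the ATRA-ATO group section, six two-week courses give 6 × 14 = 84 planned inpatient days if each course is wholly inpatient, against about 0 for RIF at home. Ten months is about 300 days. For equal means, about 84 / 300 = 28% of RIF patients would have to spend the whole window in hospital. If 10% did, the RIF mean would be 0.10 × 300 = 30 days against 84. Means and ranks would then agree on direction.

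**The case against.** The strongest reply is that the size comes entirely from assumption. No passage says that RIF costs are more skewed, and equal shapes give no excess. That stands: the percentages show a mechanism and do not forecast this trial's error rate.

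A reader might attribute the RIF tail to relapses. The documents do not support this. Sample size calculation has fewer failures with RIF ("assuming 97% DFS in the control (ATO) group, and conservatively assuming 99% DFS in the experimental (RIF) group"), which is about 0.5 against 1.6 among 53, and the costs listed are those of induction and consolidation. Any tail must come from complications during treatment.

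A reader might also infer that the normality rule decides the cost test. It does not; costs have their own sentence. The Mann-Whitney figures apply to costs only after the pairing is removed. The matched-pairs test for two independently randomised arms is a separate and plainer error. Correcting it alone would lead to Mann-Whitney under the general rule, so the present point would remain.

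The stronger reading that the plan could falsely show fewer hospital days is not realistic, given Step 7. One caution applies: the Abstract has patients continue on oral RIF after molecular remission, without separating the arms, whereas the ATRA-ATO group section continues ATO. The gap in days depends on which holds, and the two passages must be reconciled.

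It can also be said that averages will be reported descriptively, that the protocol calls the cost comparison post hoc, and that total may mean each patient's own total. These points soften the concern. They do not remove it: patients' totals still have to be summarised by arm, and the only inferential statement fixed for costs is a rank test. This is a stated choice of test, not detail left to another document.

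**Conclusion.** The point holds in a limited form. For costs, the named test does not address the quantity in the hypothesis and gives no interval for the saving. It can favour RIF at equal mean cost if RIF costs are the more skewed: about 12% to 32% for the test as written and 28% to 72% for its unpaired counterpart, against 5% to 7% for Welch. These figures assume lognormal costs, RIF CV 0.6 to 1.0, ATO CV 0.3 and 59 per arm. The excess shrinks if a variable shared induction cost makes up much of the total, and it vanishes if the shapes are equal. If the true cost gap is large, the direction of the conclusion would not change.

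For days, the loss is an estimate of days saved rather than a risk of a wrong direction. The primary comparison of disease-free survival is unaffected. The change is worth making because it aligns the analysis with the claim at almost no cost.

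**What to change.** In Statistical analysis, replace the cost sentence, and the normality-driven choice for hospitalization days, with one pre-stated main comparison for each outcome: the difference in arithmetic means between the two independent randomised arms, with a bootstrap (or Welch) 95% confidence interval. Report medians and an unpaired rank test as support only.

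This takes a few lines of wording and no new data. The downside is small: if a few patients are very costly, the interval for the mean will be wide, and Welch may run slightly above its nominal level, as the 5% to 7% shows.

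### The analysis section names only tests of no difference for DFS and not the −5-point margin test behind the sample size; the Z rule that gives 53 per group exceeds its 5% error

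*Protocol article*

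**What the plan says.** **Sample size calculation (protocol article).** "The design of this trial is a non-inferiority trial with superiority being explored if non-inferiority is identified". The inputs are "assuming 97% DFS in the control (ATO) group", "conservatively assuming 99% DFS in the experimental (RIF) group", "a noninferiority margin of − 5" points, and "follow up of 2 years, 5% type I error (one-sided), 90% power". The result is 53 evaluable patients per group, raised to 59 per group (118 in all) for 10% withdrawal.

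**Outcome measures.** The 2-year DFS rate is the primary outcome.

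**Statistical analysis.** "The primary analysis will be conducted on the intention-to-treat principle". For survival: "Survival functions will be estimated using the Kaplan-Meier method and will be compared using the log-rank test". For dichotomous and categorical variables the section names Pearson's chi-square or Fisher's exact test. On sidedness: "All statistical tests will be two-sided, and the level of significance will be set at 0.05, except for the non-inferiority hypothesis". It names no confidence bound, margin test or decision rule for the 2-year DFS difference.

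**The concern.** The sample size section poses one question: is RIF at most 5 points worse than ATO at 2 years? The tests in the analysis section answer another: is there evidence of any difference? The closing exception takes the non-inferiority hypothesis out of the two-sided 0.05 rule but puts no test in its place.

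Two things are at stake. First, with very few events expected, an equality test will nearly always be non-significant, and that result could be misread as non-inferiority. Second, plausible margin rules disagree on outcomes likely to occur here. The Blinding section says the trial is open and the analyst is not blinded, so a rule left open could be chosen after the data are seen.

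**Working it through.** **Inputs.** DFS 97% (ATO) and 99% (RIF), margin −5 points, one-sided 5%, 90% power, 53 or 59 per group, all from Sample size calculation. *Assumption:* every patient has complete 2-year follow-up, so failures are binomial.

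**1. Reproduce the stated size.** Let d = p_RIF − p_ATO, the difference in observed 2-year DFS. The unadjusted Z (Wald) rule claims non-inferiority if

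d + 0.05 > 1.645 × √[p_RIF(1 − p_RIF)/n + p_ATO(1 − p_ATO)/n].

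Power is the sum of the binomial probabilities of all outcomes that meet the rule. At 99% against 97% it is 0.857 for n = 52 and 0.919 for n = 53. So 53 is the smallest n reaching 90%, with pooled or unpooled variance. Then 53/0.9 = 58.9, rounded up to 59, and 2 × 59 = 118.

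Other routes do not give 53:
- Normal-approximation formula: (1.645 + 1.282)² × (0.99×0.01 + 0.97×0.03)/0.07² = 8.56 × 0.039/0.0049 ≈ 68.2, so 69 per group.
- Non-inferiority log-rank design: margin hazard ratio ln 0.92/ln 0.97 = 2.74, design hazard ratio ln 0.99/ln 0.97 = 0.33. Events = 4 × 8.56/[ln(0.33/2.74)]² ≈ 7.7. At a mean failure rate of 2% that is about 383 patients in total.

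The stated size therefore fits a test of a difference in proportions against the margin, and not a log-rank test.

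**2. Expected events at the design rates.**
- 59 per group: 59×0.03 + 59×0.01 = 2.36.
- 53 per group: 53×0.03 + 53×0.01 = 2.12.

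**3. What a non-significant equality test would mean.** Suppose RIF is truly at the margin (92% against 97%).

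| Two-sided 0.05 test | Non-significant, n = 53 | Non-significant, n = 59 |
|---|---|---|
| Fisher (exact enumeration) | 93% | 91% |
| Log-rank (20,000 simulated trials, exponential times, censoring at 2 years) | 80.5% | 79.4% |

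Example at 53 per group with 3 RIF and 2 ATO failures:
- d = 50/53 − 51/53 = −1.9 points.
- SE = √[(50×3)/53³ + (51×2)/53³] = 0.0411.
- One-sided 95% lower limit = −0.0189 − 1.645×0.0411 = −0.087, or −8.7 points.

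Non-inferiority is not shown, yet the two-sided chi-square p is 0.65.

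**4. Which margin rule holds 5%?** The score (Farrington–Manning/Miettinen–Nurminen) rule uses the same numerator. Its standard error is computed at the maximum-likelihood rates constrained to differ by −5 points. Exact results by enumeration:

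| Rule | Type I error (92/97), n = 53 | n = 59 | Power (99/97), n = 53 | n = 59 |
|---|---|---|---|---|
| Unadjusted Z | 9.8% | 7.5% | 0.919 | 0.908 |
| Score | 4.9% | 4.2% | 0.743 | 0.738 |

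If control DFS is 98% to 99% and RIF is 5 points lower, the Z rule's error at n = 59 is 9.2% to 12.8%.

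**5. Where the rules part (n = 59).** With 0, 1 or 2 ATO failures, the Z rule allows a claim with up to 1, 1, 1 RIF failures and the score rule with up to 0, 0, 1. Take one failure in each arm: d = 0, SE = √(2×58/59³) = 0.0238, lower limit −3.9 points. The Z rule claims non-inferiority and the score rule does not.

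**The case against.** The strongest reply is that the article already fixes the endpoint, time point, margin, alpha, sidedness and the order of non-inferiority then superiority. A one-sided 95% bound on the 2-year difference is compatible with every sentence, and the choice of interval is commonly left to a statistical analysis plan, which is not shown. Most of this stands, and it rules out several stronger readings.

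- *A reader might infer that a two-sided log-rank test is the primary non-inferiority test.* The text does not say so. The log-rank sentence is general, and the non-inferiority hypothesis is expressly exempted from two-sided testing.
- *A reader might infer that no valid non-inferiority conclusion is possible, or that a non-significant result is meant to serve as one.* Neither is stated. The design elements needed for a valid test are present.
- *A reader might infer that intention-to-treat alone is an error.* Naming it for the primary analysis does not exclude a per-protocol sensitivity analysis, which may sit elsewhere. The article gives no crossover rate from which to size a bias.

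It is also fair to say that the article names no Z or Wald interval. The link to that rule is inferred from its reproducing 53.

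What the reply does not meet is the mismatch within the article. Its analysis section lists tests by type of variable, the sidedness and the alpha, yet every test it offers for DFS is one of equality. Leaving the interval method open is also not harmless, because the rule that delivers the stated size and 90% power does not keep the stated 5% error.

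**Conclusion.** The point holds in this limited form. The analysis section names only tests of no difference for DFS, while the sample size rests on a one-sided margin test that it does not name. The stated 5% error and 90% power do not hold together at this size. The Z rule gives power of 0.919 (n = 53) or 0.908 (n = 59) at a true error of 9.8% or 7.5%. The score rule keeps the error at 4.9% or 4.2% with power of about 74%.

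These figures assume binomial outcomes with complete 2-year follow-up at the planned rates. The log-rank percentages also assume exponential failure times. The article states neither assumption. That an equality test cannot establish the margin needs no assumption.

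**What to change.** **Statistical analysis.** State the primary analysis as the difference in 2-year DFS, RIF minus ATO. Declare non-inferiority only if the one-sided 95% lower confidence limit (the lower end of a two-sided 90% interval) by a score-type method such as Miettinen–Nurminen lies above −5 points. Say how patients censored before 2 years enter, for example Kaplan–Meier rates with an effective sample size. Keep the log-rank test for the superiority look once non-inferiority is shown. Settle this before outcome data are examined.

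**Sample size calculation.** Name the test used, and restate the power under the score rule: about 74% at 53 or 59 per group under 99% against 97%.

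**Cost.** The wording is cheap. The lower stated power is the real price, and it is not slight: 0.908 to 0.738 at 59 per group. The sponsor must either accept it openly or recruit more patients. A per-protocol analysis may be added as a sensitivity analysis, but this point does not require it.

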### Randomization

Treatment allocation occurs when the study participant meets the inclusion criteria and signs the informed consent form. All eligible patients will receive ATRA-ATO for induction therapy. Participants are randomized by permuted blocks to ensure there are similar numbers of participants in the intervention and control groups. The randomization allocation schedule is generated by a statistician with no other involvement in the study. Once consented, participants are allocated in a 1:1 ratio to the two arms of the study according to a computer-generated random sequence after achieving hematologic complete remission (HCR) (Figs. 1 and 2). Participants will be informed of their allocated treatment group following randomization.

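### Medical costs are to be compared with a matched-pairs test, although the two arms are independent and no pairing is defined

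*Protocol article*

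**What the plan says.** All places are in the protocol article.

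- **Statistical analysis**, on the test: "The Wilcoxon matched pairs test will be used to compare the medical costs between the RIF and ATO groups". The same section assigns Student's t test to normally distributed variables and the Mann-Whitney U test to non-normal ones. Tests are two-sided at 0.05, apart from the non-inferiority hypothesis.
- **Statistical analysis**, on status: costs "will be compared in a post hoc analysis of the two groups".
- **Outcome measures** (text following the relapse definitions): "The secondary outcomes of this trial are hospitalization days and medical costs in the two arms". On the unit of observation: "The medical costs will be calculated for each patient".
- **Randomization**: "participants are allocated in a 1:1 ratio to the two arms of the study according to a computer-generated random sequence". On the method: "Participants are randomized by permuted blocks to ensure there are similar numbers of participants in the intervention and control groups".
- **Study hypothesis** and the abstract's Discussion both make lower medical cost with oral RIF one of the things the trial sets out to show.

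**The concern.** A matched-pairs signed-rank test works on within-pair differences, so it needs a rule that links each RIF patient to one ATO patient. No such rule is given, and parallel-group randomisation does not create one. Whoever runs the test must invent the pairs, and different pairings of the same data give different p-values. Patients left over when the arms are unequal cannot enter the test.

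The sentence also departs from the section's own rule for non-normal continuous data, and does so for costs alone. The Blinding section says that the analyst is unblinded and takes part in data collection, so an undefined pairing is a freedom best removed in advance.

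Separately, calling the comparison post hoc contradicts its listing as a secondary outcome. It would invite readers to discount a result that the trial planned from the start.

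**Working it through.** **Step 1. Set the statements side by side.** Each patient is in one arm and has one cost. Allocation is individual, 1:1, by permuted blocks whose stated purpose is similar group sizes. The article mentions no matching, crossover or pair identifier. The matched-pairs test therefore has no defined input, while the Mann-Whitney U test in the same section fits the data structure.

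**Step 2. Size of the comparison.** From Sample size calculation: 53 evaluable per group and 10% withdrawal, 53 / 0.90 = 58.9, rounded up to 59 per group. This reproduces the article's 59, which is the only one of its figures needed here.

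**Step 3. Dependence on the pairing.** The article gives no cost distribution, so lognormal costs are an assumption and two settings are shown. In each, one dataset of 59 against 59 was fixed and one arm was shuffled 5,000 times.

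| Assumed log-SD; log-mean difference | Mann-Whitney p | Signed-rank p over pairings |
|---|---|---|
| 0.5; 0.2 | 0.009 | minimum 0.0002, median 0.013, 97.5th percentile 0.039, maximum 0.113 |
| 0.6; 0.25 | 0.008 | minimum 0.00007, central 95% 0.0015 to 0.026, maximum 0.045 |

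The data are the same within each row; only the pairing changes. In the second row every pairing stayed below 0.05.

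**Step 4. Type I error at nominal 5%** (5,000 runs; Monte Carlo standard error near 5% is √(0.05 × 0.95 / 5000) = 0.3 percentage points).

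- Mann-Whitney: 5.0%.
- Signed-rank, pairs formed at random: 4.8%, not distinguishable from 5%.
- Signed-rank, both arms sorted by a covariate with assumed correlation 0.7 with cost (score = 0.7 × covariate + 0.714 × noise): 14.6%.
- Signed-rank, both arms sorted by cost itself: 77.8%, an extreme case.

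**Step 5. Power with random pairing** (log-SD 0.6). At a log shift of 0.25: signed-rank 56.6%, Mann-Whitney 59.7%, a loss of 3.1 points. At 0.35: 84.0% and 86.5%, a loss of 2.5 points.

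**Step 6. Unequal arms.** Assume that each of 59 patients per arm independently remains evaluable with probability 0.90. The probability of equal numbers is Σₖ [Bin(k; 59, 0.90)]² = 0.123. A rough check: the difference in numbers has SD √(2 × 59 × 0.9 × 0.1) = 3.26, and 1 / (3.26 × √(2π)) = 0.122. So in about 88% of trials under this assumption at least one patient would have no partner. If costs are also obtained for patients who withdraw, the loss is smaller.

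**The case against.** The strongest reply is that this is a slip for the Wilcoxon rank-sum test, which is the Mann-Whitney test under another name, and that little harm would follow in practice. Much of that stands.

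- **Validity.** A reader might infer that the p-value is simply invalid. That is too strong: with pairs formed without regard to cost or covariates the test keeps its size (4.8% above; 4.6% in a separate check with log-SD 0.5 and 10,000 runs) and loses only about 3 points of power. The inflated figures need an ordered pairing, which the article does not plan. What remains is that it states no pairing rule at all, so validity is not assured and the p-value is not unique.
- **Size of the instability.** The range 0.0002 to 0.11 gives the extremes of one dataset with a modest effect, and at least 97.5% of those pairings fell below 0.05. In a further check (20 datasets per setting, 300 pairings each), the paired test agreed with Mann-Whitney at the 0.05 level in 88% of cases at a log difference of 0.2, 99.8% at 0.35, and 100% at 0.5 and 0.7. The article's Discussion expects home treatment with RIF and hospital treatment with ATO, so a large difference is plausible, though no figure is given.
- **Permuted blocks.** A block balances numbers; the article does not present it as a source of matched pairs.
- **Induction costs.** Outcome measures says: "The hospitalization costs for induction and consolidation therapy will be calculated for inpatients". A reader might infer that costs incurred before randomisation are added into the between-arm test. The text says only that they are calculated, not that they are summed for the comparison. Total treatment cost is also a legitimate quantity, so this is no error.
- **Post hoc.** The phrase may refer to costs being worked out afterwards from hospital records. That would explain the wording, but it does not make the label correct for a listed secondary outcome.

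**Conclusion.** The concern holds in limited form: the named test is wrong for this design. Matched pairs is explicit, even if a rank-sum test was meant, and the sentence conflicts with both the design and the section's own rule. The consequences are a p-value that depends on an arbitrary choice, possible exclusion of patients, and type I error that is near 5% under random pairing but not protected otherwise (about 15% in the assumed covariate-sorted case). These sizes rest on assumed lognormal costs, an assumed correlation of 0.7 and independent 10% withdrawal; the mismatch between test and design rests on no assumption.

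The post hoc label is a second, smaller contradiction. The documents do not support reading either problem as a threat to the main result: only a secondary outcome is affected. Severity is should-fix.

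**What to change.** 1. In Statistical analysis, replace the Wilcoxon matched-pairs test for costs with the Mann-Whitney U (Wilcoxon rank-sum) test already named there.
2. In the same section, delete the post hoc label, so that it agrees with the listing of costs as a secondary outcome. If the intended meaning is that costs are extracted from records after treatment, say that instead.

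Both are wording changes to make before analysis. They need no new data and no change to design or sample size.

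Two optional suggestions, neither correcting an error: report the difference in mean cost per patient with a bootstrap 95% confidence interval; and, since all patients have the same induction regimen before randomisation, base the between-arm comparison on costs from randomisation and describe induction costs separately.
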